### COVID-19 safe data collection

We have designed a method of data collection that is both COVID-19 safe and compatible with the realities of providing care during labour and birth. Data will be entered directly into a REDCap database using an iPad specifically configured with the REDCap mobile application for the trial. Participants will carry a card that contains a unique study number that once entered will link to an existing database entry. Following randomisation the attending midwife will enter minimal required data (e.g. allocation code, results of most recent vaginal examination). The iPad will then be placed in a waterproof protective sleeve that will allow the woman to use touch screen ‘sliders’ to indicate their level of pre–treatment, injection and post-treatment on a 100 mm VAS scale. The use of digital VAS has been validated against paper versions [31]. The protective sleeve will prevent device contamination from body fluids, shower and bath water and can be disposed of following data entry. Direct data entry will reduce data transcription errors contributing to trial fidelity. Each midwife will have a unique code to identify them as responsible for data entry in keeping with Good Clinical Practice (GCP) principles. A horizontal VAS is used to measure the primary outcome, the experience of self-reported pain scores. The VAS is sensitive to pain intensity, validated for use in research and most individuals have no difficulties using it [32]. Demographic and clinical data will be extracted from the research sites perinatal database.

### Data management

Data entry, both paper and electronic, will be stored and maintained at the University of Queensland as specified by the relevant UQ Policies and Procedures, specifically: 4.20.06 Research Data Management, 6.40.01 Information Management Policy. Paper files will be stored within a locked cabinet with a locked office with only relevant research team members provided with access. Electronic files will be stored on a secure password protected network with access restricted to relevant research team members. Data sharing arrangements will specify transfer of required data using secure password protected files and file transfer platforms or restricted access to cloud based datasets (REDcap). The final dataset will only be accessible to investigators participating in the data analysis as specified within the trial agreements.

### Data analysis

All women who underwent randomisation and for whom primary outcome data is available will be analysed in their allocated treatment groups regardless of the intervention received (i.e. intention to treat). Randomisation should ensure that any baseline differences between groups occur by chance. To control for cluster effect repeated measurement, a linear mixed-model analysis will be conducted to investigate the difference in mean VAS score pre and post intervention. Missing VAS data will be addressed through imputation (last observation carried forward) A sensitivity analysis will be conducted following imputation to assess any effect on findings. Clinical data will be analysed on an available case basis with numbers of participants with missing data presented in the results tables. Categorical data will be analysed with chi-squared tests and non-repeated continuous variables will be analysed with t-tests if normally distributed or Mann-Whitney U test if non-normally distributed. Additional multivariable analysis will be employed if baseline differences are noted between the two groups. Treatment effects will be presented as mean difference or relative risks with 95% confidence intervals. All study outcomes will be analysed using a two-sided *P* value of < 0.05 to indicate statistical significance. We do not plan to undertake any subgroup analysis or interim analysis.

For the postnatal survey data descriptive statistics will be calculated for all variables, including mean, median, standard deviation, range, and percentages as appropriate. Free text responses will be analysed thematically.

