### Outcomes

The primary outcome for the trial is the mean difference in VAS scores of labour pain between intervention and control groups at 30 min following the administration of the injections. Secondary outcomes include the number of women experiencing an at least 30% or 50% reduction in pain following the injections. This is the measure of analgesic effectiveness recommended in the Cochrane Review of water injections for back pain in labour [29]. Other secondary outcomes are detailed in Table 1.

**Table 1 Tab1:** Schedule of enrolment, interventions and assessments

		Study period					
			Post-allocation				Close-out
	Enrolment	Allocation	*Time periods after injection*			*1–14 days post birth*	*From perinatal database*
TIMEPOINT**			*30 min*	*60 min*	*90 min*		

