### Participant retention and completion of follow-up

As the primary and clinical outcomes data is collected prior to or at birth loss to follow-up is expected to be minimal. Therefore, there are no specific plans to promote participant retention beyond this timeframe. Reasons for discontinuing the injections or declining further rounds of injections (i.e. birth, progress to use of epidural, other maternal reason, other fetal reason (e.g. abnormal CTG)) will be collected by the midwife on the data collection form. For women who remain in hospital following their birth the survey will be completed on a tablet device. For those women opting for early discharge or discharged on weekends, a link to the survey will be emailed with one follow up contact from a research assistant within 2 weeks.

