### Sample size

We have calculated the sample size based on the recommended minimal clinically significant reduction in VAS scores: 10 mm difference on a 100 mm VAS score between intervention and placebo [30]. To demonstrate a 10 mm reduction (SD 20 mm) in VAS scores with 80% power and 0.05 significance (two-sided) would require 64 participants per group. Based on previous studies [15] we estimate an attrition of 20% due primarily to women giving birth or requesting epidural analgesia prior to the measurement of the primary outcome. The total sample size required would be 154 participants, 77 per trial group.

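### The set labelled intention to treat is an available-case set that omits about 20% of randomised women, and the imputation rule does not say whether it brings them back

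*Protocol article*

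**What the plan says.** All references are to the protocol article.

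- **Outcomes.** The primary outcome is the mean difference in labour-pain VAS "between intervention and control groups at 30 min following the administration of the injections". The proportions with at least a 30% or 50% reduction in pain are secondary outcomes, placed at 30 minutes in Table 1.
- **Data analysis, set.** "All women who underwent randomisation and for whom primary outcome data is available will be analysed in their allocated treatment groups", and this is done "regardless of the intervention received (i.e. intention to treat").
- **Data analysis, missing scores.** "Missing VAS data will be addressed through imputation (last observation carried forward"). No time point is named. The next sentence adds: "A sensitivity analysis will be conducted following imputation to assess any effect on findings". Its content is not described.
- **Sample size.** The calculation allows for an "attrition of 20% due primarily to women giving birth or requesting epidural analgesia prior to the measurement of the primary outcome".
- **Participant retention and completion of follow-up.** Here the stated expectation is different: "As the primary and clinical outcomes data is collected prior to or at birth loss to follow-up is expected to be minimal".

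**The concern.** Intention to treat has two parts: women are analysed in the arm to which they were allocated, and all randomised women are included. The Data analysis sentence secures the first and gives up the second, because membership of the set depends on something that happens after randomisation. The protocol itself names the two main reasons for a missing score. In an analgesia trial, an epidural request within 30 minutes of the injections is plausibly a sign that they did not give enough relief. Leaving such women out can therefore remove treatment failures from the primary mean and from the responder proportions, while the report would describe the analysis as intention to treat.

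The imputation rule adds a second difficulty. If the set is taken literally, no 30-minute score is missing and there is nothing to impute at that time. If the rule is meant to apply at 30 minutes, the set sentence cannot stand. Depending on which sentence is followed, the primary result rests on about 123 or on 154 women.

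**Working it through.** **Inputs from the protocol.** Difference 10 mm, SD 20 mm, 80% power, two-sided 0.05, 64 per group, 20% attrition, 154 in total or 77 per group (Sample size). Pre-injection pain of at least 60 mm (Eligibility criteria). Labour-pain VAS before the injections and at 30, 60 and 90 minutes (Table 1).

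**1. The plan's own figures.** n per group = 2 × (1.96 + 0.84)² × (20/10)² ≈ 63 by the normal formula and 63.8 by the t-test, so 64 reproduces. 64 × 1.2 = 76.8, so 77 per group and 154 in total also reproduce. (Dividing by 0.8 would give 80 per group and 160. That is a separate, minor matter.)

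**2. Women outside the set.** 154 × 0.20 = 30.8, about 31. This leaves 154 − 30.8 = 123.2, or 61.6 per group. Power at 61.6 per group is about 79%, so the loss of precision is small. The issue is bias.

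**3. Available-case mean difference (assumed values).** Suppose the true difference is 10 mm. Let a share p of an arm be missing, and let the missing women's 30-minute pain be g mm higher than that of the observed women. The observed arm mean is then the true mean minus p × g. With the same g in both arms, the available-case difference is 10 − g × (p_saline − p_water).

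| Loss, saline / water | g = 10 mm | g = 20 mm | g = 30 mm |
|---|---|---|---|
| 20% / 20% | 10 | 10 | 10 |
| 25% / 15% | 9 | 8 | 7 |
| 30% / 10% | 8 | 6 | 4 |
| 15% / 25% | 11 | 12 | 13 |

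The protocol gives neither g nor the loss by arm, so the table shows a range and predicts nothing.

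**4. Responder proportions (assumed values).** Take 50% responders on water and 35% on saline among women with a score: risk ratio 0.50/0.35 = 1.43. Now count women lost through early epidural as non-responders.

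- 10% lost on water and 20% on saline: 0.50 × 0.90 = 0.45 and 0.35 × 0.80 = 0.28, risk ratio 1.61.
- Loss rates reversed: 0.50 × 0.80 = 0.40 and 0.35 × 0.90 = 0.315, risk ratio 1.27.

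The shift can go either way.

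**5. Carrying forward at 30 minutes.** Table 1 has no labour-pain score between the injections and 30 minutes, and the injection-pain VAS measures something else. The last observation is therefore the pre-injection score, which means no change. With 20% missing in each arm, a 10 mm effect among women with a score and equal pre-injection means, the difference is 0.80 × 10 + 0.20 × 0 = 8 mm. Power at 77 per group is Φ(8 / (20 × √(2/77)) − 1.96) = Φ(0.52) ≈ 70%, with the SD of 20 mm assumed unchanged.

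**6. The two statements on loss.** The retention section names the primary outcome among the data for which it expects minimal loss. The Sample size section expects one woman in five to lack that same outcome.

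**The case against.** The strongest reply is that the text allows a coherent reading. Carrying forward may be meant only for 60 and 90 minutes, or only for the planned sensitivity analysis, and a statistical analysis plan that is not shown may say so. That stands in part: the imputation point is an ambiguity, and it would go too far to say that the protocol states two rival primary sets. It does not rescue the label, which is something the protocol states, not something it leaves to another document.

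Loss to follow-up can also mean a woman who cannot be reached, as distinct from one who gave birth or requested an epidural before the score was due. Because the retention sentence names the primary outcome, the two sections still need to be aligned.

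A reader might infer three stronger things that the documents do not support:

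- **Birth, analgesia-use and neonatal comparisons also lose these women.** The Data analysis section gives clinical data its own available-case rule, and Table 1 takes the birth and neonatal outcomes from the perinatal database.
- **No retention effort is planned.** The retention section limits that statement to the period after the primary and clinical data are collected. It also has midwives record reasons for discontinuing and provides one follow-up contact for the survey.
- **Failures leave faster in the less effective arm.** This is plausible but undocumented. The 20% is not split by arm or between births and epidural requests, and a birth before 30 minutes is not evidently a treatment failure.

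Finally, a woman with only a pre-injection score adds almost nothing to the 30-minute contrast in a mixed model, and such a model does not correct loss that depends on unobserved pain. This is right, and it limits what redefining the set can achieve alone.

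**Conclusion.** The point holds. The set is an available-case set under an intention-to-treat label, and by the protocol's own estimate it leaves out about 31 of 154 women, partly for a reason plausibly linked to the outcome. The primary mean difference and the responder proportions may be biased. Direction and size are unknown, and if loss and the pain gap are equal in both arms the mean difference is not biased. The figures of 4 to 13 mm for a true 10 mm, and risk ratios of 1.27 to 1.61 against 1.43, rest on assumed loss rates and pain gaps.

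The scope of the imputation must be settled, because using it at 30 minutes would reduce a 10 mm effect to about 8 mm under the stated assumptions. The protocol's own minimal clinically significant difference is 10 mm, so this choice could move the estimate across that threshold. The two statements on expected loss disagree and should be reconciled.

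**What to change.** - **Set.** Define the primary set as all randomised women by allocated arm. Otherwise call it an available-case set and drop the intention-to-treat label. Do not rely on women with only a pre-injection score entering the mixed model to remove the bias.
- **Imputation.** State whether last observation carried forward applies at 30 minutes, only at 60 and 90 minutes, or only in a sensitivity analysis.
- **Data collection.** Keep asking for the 30-minute VAS after an epidural request, and flag scores taken after an epidural. State how flagged scores enter the primary mean, since the responder outcomes below treat the same event differently.
- **Responder outcomes.** Use all randomised women as the denominator and count an epidural before 30 minutes as non-response. Report births before 30 minutes separately, with sensitivity analyses counting them both ways.
- **Reporting.** Give the number of missing 30-minute scores and the reasons, by arm.
- **Consistency.** Reword the retention section to agree with the 20% in the Sample size section.

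The cost is changes of wording, one instruction to midwives, slightly more analysis work, and some flagged post-epidural scores that are harder to interpret. The planned sample size is not altered by this point.

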**Methods:**

In this pragmatic, placebo controlled trial 154 low-risk women in labour at term with a labour pain score ≥ 60 on a 100 millimitre visual analogue scale (VAS) will be randomly allocated to receive either six injections of sterile water or a sodium chloride 0.9% solution as a placebo (0.1–.0.3 ml per injection). Three injections are given along the midline from the fundus to the supra-pubis and three laterally across the supra-pubis. The primary outcome will be the difference in VAS score 30 min post injection between groups. Secondary outcomes include VAS score of the injection pain on administration, VAS score of labour pain at 60 and 90 min, maternal and neonatal birth outcomes.

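### The mixed-model sentence names a pre-versus-post contrast, not the between-group VAS difference at 30 minutes that is the primary outcome, and ties baseline adjustment to observed imbalance

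*Protocol article*

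**What the plan says.** The protocol article describes the primary comparison in four places.

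- **Abstract, Methods:** "The primary outcome will be the difference in VAS score 30 min post injection between groups".
- **Outcomes:** the primary outcome is the "mean difference in VAS scores of labour pain between intervention and control groups at 30 min following the administration of the injections". Table 1 schedules post-injection labour-pain VAS at 30, 60 and 90 minutes; the Abstract makes 60 and 90 minutes secondary.
- **Sample size:** the target is a "10 mm difference on a 100 mm VAS score between intervention and placebo", and "To demonstrate a 10 mm reduction (SD 20 mm) in VAS scores with 80% power and 0.05 significance (two-sided) would require 64 participants per group".
- **Data analysis:** to handle repeated measurement, "a linear mixed-model analysis will be conducted to investigate the difference in mean VAS score pre and post intervention".

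The same Data analysis paragraph says that women are analysed in the group to which they were allocated and that treatment effects are given as mean differences or relative risks with 95% confidence intervals. It keeps t-tests and Mann-Whitney tests for continuous variables that are not measured repeatedly. It adds multivariable analysis only if differences between the groups are noted at baseline.

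**The concern.** The only analysis named for the repeated VAS states its target as pre against post. That is a comparison over time, whereas the primary outcome is a comparison between arms at one time. Nothing else in the paragraph supplies the missing contrast: the t-test rule excludes repeated variables, and the statement on treatment effects is not linked to the mixed model or to 30 minutes.

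The distinction matters because a fall in VAS is to be expected in both arms. Women are randomised only when they score at least 60 mm and ask for pain relief, so some regression towards the mean is likely. The Randomisation and blinding section itself calls saline an active placebo with some analgesic effect. A pre-post change therefore cannot by itself show that water is superior.

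Even if a group comparison is taken for granted, the sentence leaves three candidates open: the 30-minute difference, the difference in change from baseline, and a difference averaged over 30, 60 and 90 minutes. The third is a different estimand. The first two share an expected value under randomisation but differ in precision. Letting baseline adjustment depend on observed imbalance leaves one more choice to be made after the data have been seen.

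**Working it through.** **1. What the sample size rests on.** Inputs from Sample size: difference 10 mm, SD 20 mm, two-sided 0.05, power 80%. Normal approximation: n per group = 2 × (1.960 + 0.842)² × 20² / 10² = 62.8, so 63. The two-sample t-test gives 63.8, so 64, with power 80.1% at 64 per group. The stated 64 is reproduced, and it is a comparison of two group means, not a pre-post test.

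**2. What the literal pre-post contrast would test.** Suppose water and saline are equally effective and VAS falls by d in both arms. Pool 128 women. Probability of significance = Φ(d / (SD_change / √128) − 1.960). The pre-injection SD and the correlation r between pre-injection and 30-minute VAS are not in the article; assume a pre-injection SD of 10 to 13 mm (justified in step 3), a 30-minute SD of 20 mm and r = 0.3. Then SD_change is 19.5 to 20.3 mm.

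- d = 5 mm: 79% to 83%.
- d = 10 mm: above 99%.

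So this contrast would usually be significant with no treatment effect at all.

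**3. Change score against baseline adjustment.** Let s₀ be the pre-injection SD and s₁ = 20 mm the 30-minute SD.

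- Change score: SD_change = √(s₀² + s₁² − 2·r·s₀·s₁)
- Baseline-adjusted: SD_adj = s₁·√(1 − r²)

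Eligibility requires VAS of at least 60 on a scale that ends at 100, so pre-injection scores should lie within a 40 mm range. The largest SD on that range is 20 mm, reached only if half the women score 60 and half score 100. A uniform spread gives 40/√12 = 11.5 mm. An s₀ of 10 to 13 mm is taken as a plausible range around that value.

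Power by t-test, 64 per arm, 10 mm difference:

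| r (assumed) | SD_change, s₀ = 10 / 13 | Change-score power, s₀ = 10 / 13 | SD_adj | Adjusted power | Gain from adjusting |
|---|---|---|---|---|---|
| 0.2 | 20.5 / 21.6 | 78% / 74% | 19.6 | 82% | 4 / 8 points |
| 0.3 | 19.5 / 20.3 | 82% / 79% | 19.1 | 84% | 2 / 5 points |
| 0.5 | 17.3 / 17.6 | 90% / 89% | 17.3 | 90% | 0 / 1 point |

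Adjustment is never worse than the change score here. They tie when r·s₁ = s₀, as at r = 0.5 with s₀ = 10.

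**4. The extreme case.** With s₀ = 20 mm, the change score has power of 60%, 66% and 80% at r = 0.2, 0.3 and 0.5. That needs the two-point distribution described in step 3.

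**The case against.** **A pooled pre-post test is not a realistic reading.** The article describes a placebo-controlled superiority trial, analyses women by allocated group, reports treatment effects, and elsewhere defines the VAS result between groups. This stands. The figures in step 2 show why the wording should not be followed literally; they do not predict what the investigators will do.

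**Under the sensible reading the estimand is unaltered.** Randomisation makes the expected between-arm difference in change to 30 minutes equal to the expected difference at 30 minutes. A mixed model of pre and post scores with a group-by-time term targets the same quantity and, with baseline means constrained equal, has essentially the efficiency of baseline adjustment. This also stands, but the sentence specifies neither the term nor the time point.

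**Model detail belongs in the analysis plan.** True of covariance structure and similar matters, and their absence is not criticised here. The point is that the contrast which the article does state disagrees with its own primary outcome.

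**Two stronger readings are tempting and not supported.** A reader might infer that a change-score analysis would forfeit much of the planned power. That requires the maximum possible pre-injection SD; with a plausible SD the shortfall against adjustment is 0 to 8 points, and at r = 0.3 the change score keeps roughly the planned 80%. A reader might also infer that the SD of 20 mm belongs to a different quantity from the one analysed. The Sample size section does not say whether it is the SD of a single score or of a change, so no mismatch is shown.

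**Conclusion.** The concern holds as a misstated primary contrast. The Data analysis sentence names pre versus post; the Abstract, Outcomes and Sample size sections require a between-group difference, which the first two place at 30 minutes. This conclusion comes from the text alone and needs no assumption about correlation or SD. Conditional adjustment for baseline is a second, smaller defect in the same paragraph, because it lets the data decide the form of the model.

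The consequence for precision is modest: about 0 to 8 power points in favour of prespecified adjustment over a change score, assuming a pre-injection SD of 10 to 13 mm, a 30-minute SD of 20 mm and correlations of 0.2 to 0.5. An unseen analysis plan may already contain the right model; the published sentence would still disagree with it and should be corrected.

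**What to change.** Replace the mixed-model sentence with wording to this effect: the primary analysis is a linear mixed model of labour-pain VAS at 30, 60 and 90 minutes, with arm, time, arm-by-time and pre-injection VAS as a prespecified covariate, allowing for correlation within women. The primary result is the water-minus-saline difference at 30 minutes with its 95% confidence interval; the 60- and 90-minute differences are secondary. State that adjustment for pre-injection VAS is made whether or not imbalance is observed, and limit the clause on multivariable analysis after noted baseline differences to supportive analyses.

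The cost is a few lines of text, to be settled before unblinding. Pre-injection VAS is already collected according to Table 1, no extra assessment is needed, and the requirement of 64 evaluable women per group is unchanged.

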### Eligibility criteria

Eligibility criteria consists of ≥16 years of age, singleton cephalic (head down) pregnancy, ≥ 37 weeks gestation, spontaneous or induced labour, no serious concurrent medical conditions (pre-eclampsia, coagulopathy, diabetes other than diet controlled), cognitively capable of providing consent, able to read and understand instructions written in English. Upon admission to the birth suite randomisation will occur when the participant’s self-assessment of labour pain ≥60 mm (Visual Analogue Scale [VAS] 0-100 mm, 0 = no pain 100 = worst conceivable pain), and requesting pain relief.

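### The analysis text both excludes and imputes women with no 30-minute VAS, and last observation carried forward would score them as having no relief

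*Protocol article*

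**What the plan says.** All references are to the protocol article.

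- **Outcomes.** The primary outcome is the "mean difference in VAS scores of labour pain between intervention and control groups at 30 min following the administration of the injections".
- **Table 1.** Labour-pain VAS is scheduled before the injections and at 30, 60 and 90 minutes. No labour-pain score falls between the first two.
- **Eligibility criteria.** "randomisation will occur when the participant’s self-assessment of labour pain ≥60 mm", so the pre-injection score is high by design.
- **Sample size.** The authors expect "attrition of 20% due primarily to women giving birth or requesting epidural analgesia prior to the measurement of the primary outcome" and enlarge the trial to cover it.
- **Data analysis, opening sentence.** The analysis takes in randomised women whose primary outcome was obtained, in their allocated arms, and calls this intention to treat.
- **Data analysis, later.** A linear mixed model is planned for the repeated VAS scores. Then: "Missing VAS data will be addressed through imputation (last observation carried forward". No time point is exempted. A sensitivity analysis after imputation is planned, without stated content.

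**The concern.** A woman who gives birth or has an epidural before 30 minutes falls under both rules. The opening sentence leaves her out; the imputation sentence fills her in. The text does not say which prevails, so the primary analysis set is not fixed for about one woman in five.

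Neither answer is satisfactory.

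- **If she is imputed,** the last observation is her pre-injection score, so her recorded change is exactly zero. That is not a plausible 30-minute value once contraction pain has ended with birth or has been treated by an epidural. She would also count automatically as a non-responder for the 30% and 50% reduction outcomes. The same VAS difference feeds the economic analysis.
- **If she is excluded,** the comparison is conditioned on events after randomisation and is not full intention to treat. LOCF then still applies at 60 and 90 minutes, where it holds pain constant while labour progresses.

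Wherever LOCF is used, single imputation treats filled-in values as if they had been measured.

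**Working it through.** **1. The plan's own figure.** Inputs from Sample size: difference 10 mm, SD 20 mm, two-sided 0.05, 80% power. The t-test calculation gives 63.8, so 64 per group (power 80.1%), as stated. The total follows as 64 × 1.2 = 76.8, so 77 per group and 154 in all.

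**2. Comparator without LOCF.** With 20% missing, 77 × 0.8 = 61.6 per arm are observed. The standard error is 20 × √(2/61.6) = 3.60 mm. 10/3.60 − 1.96 ≈ 0.81, so power is about 79% (78.6% by the t-test).

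**3. Effect of LOCF at 30 minutes.** Let m_w and m_s be the proportions missing on water and saline, b the mean carried pre-injection score, μ the saline mean at 30 minutes among women observed, and δ the effect among women observed. Each arm's mean is (1 − m) × observed mean + m × b, so

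expected difference (saline − water) = (1 − m_w) × δ + (m_s − m_w) × (b − μ).

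Variance per arm = (1 − m) × 20² + m × 12² + m(1 − m) × (b − observed mean)², with 77 per arm.

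Assumptions not in the documents: b from 70 to 80 mm, pre-injection SD 12 mm, μ from 50 to 70 mm. The central case is b = 80, saline 65, water 55. The missingness by arm is also assumed; the protocol gives only the overall 20%.

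*Equal missingness.* The second term vanishes: 0.8 × 10 = 8.0 mm, whatever the means. In the central case the variances are 320 + 28.8 + 0.16 × 25² = 448.8 (water) and 320 + 28.8 + 0.16 × 15² = 384.8 (saline). The standard error is √(833.6/77) = 3.29 mm, and power is about 68%.

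*True effect 10 mm:*

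| Missing, water / saline | Central case | Range of difference | Range of power |
|---|---|---|---|
| 20% / 20% | 8.0 mm, 68% | 8.0 mm | 56% to 75% |
| 25% / 15% | 7.5 − 0.1 × 15 = 6.0 mm, 44% | 4.5 to 7.5 mm | 22% to 69% |
| 15% / 25% | 8.5 + 0.1 × 15 = 10.0 mm, 86% | 8.5 to 11.5 mm | 80% to 87% |

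*No true effect* (δ = 0; b from 75 to 80, both arms at 60 to 50). The difference is (m_s − m_w) × (b − μ), with b − μ from 15 to 30 mm:

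- Equal missingness: 0.
- 15% water / 25% saline: 0.1 × 15 to 0.1 × 30 = 1.5 to 3 mm in favour of water. The chance of a significant result for water is about 7% to 13%.
- 10% water / 30% saline: 0.2 × 15 to 0.2 × 30 = 3 to 6 mm, chance about 16% to 40%.

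The nominal chance in that direction is 2.5%. With the loss reversed, the spurious difference favours saline.

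**The case against.** The strongest reply is that LOCF may never reach the primary outcome. The analysis-set sentence requires an observed primary outcome, and Sample size counts early birth and epidural as attrition and recruits extra women to cover them, which makes sense if they leave the primary comparison. On that reading LOCF affects only 60 and 90 minutes, and the 30-minute figures above do not arise. This stands as a possible reading. A reader might infer that the primary result is certain to be biased by LOCF, but the documents do not establish that. They do establish that two sentences of one section disagree.

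A reader might also infer a known direction of bias. The documents give no missingness by arm. If epidural requests follow failed relief and water works, saline should lose more women; in the 15% / 25% central case the two terms cancel and the difference stays at 10 mm. If water does not work, that mechanism alone predicts equal loss and no spurious effect. The unequal cases show sensitivity, not a forecast.

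Carrying the pre-injection score forward after an epidural can be defended as deliberately scoring treatment failure. The protocol does not present it so, and the argument does not extend to birth.

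Finally, a sensitivity analysis is planned, and a condensed article may leave its content to the full protocol. That is fair, but a sensitivity analysis does not repair a poorly chosen primary rule.

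**Conclusion.** The point holds in conditional form. The Data analysis section gives conflicting rules for women without a 30-minute VAS, and LOCF is a poor rule wherever it is applied.

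If it is applied at 30 minutes with 20% missing in each arm, a 10 mm effect becomes 8 mm. That dilution is algebraic and does not depend on the assumed means. Power falls from about 79% to about 68% in the central case, a loss of roughly 11 percentage points; the 56% to 75% range does rest on the assumed means. With unequal missingness the bias can go either way, from 4.5 mm to 11.5 mm for a true 10 mm in the 25/15 and 15/25 splits. With no true effect, greater loss on saline gives a spurious benefit of about 1.5 to 6 mm.

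If these women are excluded, the 30-minute dilution does not occur. What remains is departure from full intention to treat and frozen scores at 60 and 90 minutes. The planned mixed model handles incomplete series without single imputation, so nothing requires LOCF.

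**What to change.** 1. Delete LOCF.
2. Make the planned linear mixed model the primary analysis, fitted to all observed VAS scores including the pre-injection score, in all randomised women with any VAS, without single imputation. The treatment contrast at 30 minutes is the primary estimate.
3. Rewrite the analysis-set sentence to agree with this.
4. State how the analysis treats birth before 30 minutes and, separately, epidural before 30 minutes. Deleting LOCF does not by itself settle this.
5. Make the planned sensitivity analysis a multiple-imputation delta-shift analysis by reason for missingness.

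The cost is wording and some code. The protocol already plans to record why injections were discontinued or declined, with birth and epidural among the reasons; the trial should check that this also identifies why a VAS score is missing.

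There is one small downside. The mixed model assumes data are missing at random, so a woman with only a pre-injection score is in effect given the relief typical for her arm. That is doubtful after birth or an epidural, which is why items 4 and 5 are needed alongside item 2.
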